### **8.7 Concomitant Interventions (treatments)**

Co-administration of the anti-diabetic drug metformine with dolutegravir increases the plasma concentration of metformine; a dose adjustment of metformine is needed with limiting total daily dose to 1000 mg. As metformin is eliminated renally, patients with moderate renal impairment may be at

increased risk for lactic acidosis due to increased metformin concentrations. Therefore, blood glucose and kidney function will be screened in diabetic patients under metformine at the start and during co-administration with dolutegravir + emtricitabine dual therapy, i.e. week 6, 12, 24 and 36. If creatinine clearance falls below 45ml/min, metformine will be stopped as per Swiss endocrinology and diabetology guidelines (94) and a switch to another oral antidiabetic drug will be made and documented in the study CRF.

Participants receiving magnesium-, aluminium- or calcium-containing anti-acids or vitamin supplements with calcium, iron, or magnesium will take dolutegravir 2 hours before or 6 hours after co-administered drugs.

Concurrent participation in non-interventional clinical trials is allowed as long as there is no impact on the objectives of this trial.

## **8.8 Study Drug Accountability**

Study centre distributing ARV will order its own study drugs using the hospital's supply route. The ARV drug bottles will be labelled with study specific labels. Participants will be asked to return ARV drug bottles (full, partially empty and completely empty) to the study nurse at each visit occurring at the SHCS center. The study sites will maintain adequate documentation of the ARV drug distribution. Sample documentation will be provided by the Sponsor-Investigator. This applies to the interventional product as well as the comparators.

## **8.9 Return of Study Drug**

Returned drugs bottles (full, partially empty and completely empty) will be registered in individual patient's files.

# **9. STUDY ASSESSMENTS**

## 9.1 Study flow chart(s) / table of study procedures and assessments

|                                                                    | Screening              | Year 1         |                |                |                |                |                |
|--------------------------------------------------------------------|------------------------|----------------|----------------|----------------|----------------|----------------|----------------|
|                                                                    | -4 weeks to
-1 week | Day 0          | Week 6         | Week 12        | Week 24        | Week 36        | Week 48        |
| Eligibility screen                                     | X                      | X              |                |                |                |                |                |
| Written informed consent                                           | X                      |                |                |                |                |                |                |
| Demographics                                                       | X                      |                |                |                |                |                |                |
| HIV-related data and medical history                   |                        | X              |                |                |                |                |                |
| Concomitant medications                                |                        | X              | X              | X              | X              | X              | X              |
| Full physical examination by physician                 |                        | X              |                |                | X              |                | X              |
| Allocation (double randomization)                                  |                        | X              |                |                |                |                |                |
| Start DTG + FTC OR remain on standard cART                         |                        | X              |                |                |                |                |                |
| Start patient-centered monitoring OR remain on standard monitoring |                        | X              |                |                |                |                |                |
| Adherence check                                                    |                        | X              | X              | X              | X              | X              | X              |
| Adverse events check                                               |                        | X              | X              | X              | X              | X              | X              |
| Drug distribution                                                  |                        | X              | X              | X              | X              | X              | X              |
| HIV-RNA in plasma + sample storage                                 | X          | X B | X B | X B | X B | X B | X B |
| HIV-DNA in plasma (in batch)                                       |                        | X              |                |                |                |                | X              |
| CD4 count*                                                         | X                      |                |                | X*             | X*             | X*             | X              |

Columns with purple background represent visits which need to be performed at site

 At screening visit: patient chart review for exclusion and inclusion criteria. At day 0: review of laboratory assessments made at the screening visit and completion of the eligibility checklist.

 At day 0: HIV-1 infection, date of HIV-1 diagnosis, years of HIV-1 suppression, nadir CD4 count, zenith HIV-1 RNA, previous genotype, ongoing hepatitis B and C, other co-morbidities. All other visits: updated medical history including changes or additions to diagnoses, diseases and medications will be done in the frame of the concomitant medication and the adverse event check.

 Prohibited: carbamazepine, oxcarbamazepine, phenytoin, phenobarbital, St John's wort and rifampicin.

 Full physical examination by study nurse & medical doctor: vital signs, anthropometric measurements, cardiovascular, respiratory and gastrointestinal systems; central nervous and skin systems as deemed necessary.

 No sample storage on screening visit

|                                                                                                                            |   |   |                                                                                     |     |     |     |   |
|----------------------------------------------------------------------------------------------------------------------------|---|---|-------------------------------------------------------------------------------------|-----|-----|-----|---|
| Full blood count*                                                                                                          | X |   |                                                                                     | X*  | X*  | X*  | X |
| Safety serum chemistry 6 *                                                                                      | X |   | ‡μ                                                                                  | X*μ | X*μ | X*μ | X |
| Urine Beta HCG pregnancy test in women with childbearing potential if applicable                                           | X |   |                                                                                     |     | X   |     | X |
| HIV RNA in plasma and sample storage                                                                                       |   | X | (at any time if HIV-RNA is ≥ 100 copies)                                            |     |     |     |   |
| Genotypic resistance test (real time) and pharmacogenetic analysis (en batch)                                              |   |   | (at any time if HIV-RNA is ≥ 100 copies on two consecutive measurements)            |     |     |     |   |
| DTG and FTC plasma concentration                                                                                           |   |   | (at any time if HIV-RNA is ≥ 100 copies, if twice consecutively only at first time) |     |     |     |   |
| Health-related quality of life questionnaire PROQOL-HIV                                                                    |   | X |                                                                                     | X   |     |     | X |
| Visual analog scale                                                                                                        |   | X |                                                                                     | X   |     |     | X |
| Assess willing for change of monitoring option / satisfaction if patient randomised in the patient-centered monitoring arm |   |   |                                                                                     | X   | X   | X   | X |
| Health related costs assessment                                                                                            |   |   |                                                                                     |     |     |     | X |

 Safety serum chemistry includes CK, creatinine, ASAT, ALAT, gamma-GT, alkaline phosphatases; glucose and lipid profile.

β Patients with HIV-RNA between 20 and 99 copies/ml will benefit from another HIV-RNA measurement after 6-4 weeks (± 5 days).

\* CD4-count, full blood count and safety serum chemistry will be performed on a 3-monthly basis for patients randomized in the standard monitoring arm. Patients randomized in the patient-centered monitoring arm will benefit from these routine tests on a yearly basis (i.e. at day 0 and week 48).

‡ Patients new to DTG will benefit from CK measurement and from hepatic safety serum tests, i.e. ASAT, ALAT, gamma-GT, alkaline phosphatases, at week 6 whatever monitoring arm.

μ Diabetic patients under concomitant metformine and dolutegravir will benefit from blood glucose and creatinine measurements at weeks 6, 12, 24 and 36 whatever monitoring arm.

## 9.2 Assessments of outcomes

### 9.2.1 Assessment of Primary Outcomes

- Viral load in plasma: HIV-1 RNA level in the plasma will be measured at every study-visit. HIV-1 RNA levels will be quantified using PCR with a limit of detection of 20 copies/ml or less at local virology laboratories. The same assays are being used for and recognised by the SHCS.
- Costs: costs will be measured starting from the baseline visit for the complete study period and from the perspective of the health care provider. Costs will be obtained from health-care insurance of the participants and from trial accounting and collected at week 48. We will consider the following costs:
  - Costs of outpatient medical consultations (HIV and non-HIV medical consultations);
  - Costs of other consultations (non-medical consultations);
  - Costs of antiretroviral drugs;
  - Costs of other drugs;
  - Costs of laboratory tests;
  - Costs of diagnostic tests other than laboratory;
  - Costs of hospitalization;
  - Costs related to the study;
  - Other costs.

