### **8.5 Data Collection and Follow-up for withdrawn participants**

Participants who withdraw from the study will be asked to come in for a close-out visit (named study discontinuation visit) where all assessments planned at week 48 will be done.

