**9.3.7. Week 48 ( $\pm 21$  days) or study discontinuation visit at SHCS center:**

*Clinical assessments:*

- Questionnaires completion: visual analog scale, PROQOL-HIV
- Adherence session by the study nurse;
- Recording/update of concomitant medications;
- Adverse event recording;
- Physical examination and vital signs;
- Study drug return (DTG + FTC or standard cART).
- Patient's monitoring satisfaction.

*Laboratory assessments:*

- HIV-1 RNA in plasma;
- CD4 count;
- Full blood count;
- safety serum chemistry: CK, creatinine, ASAT/ALAT, gamma-GT, alkaline phosphatases, glucose and lipid profile;
- Plasma and cells sample storage;
- HIV-1 DNA from PBMCs by ddPCR (performed retrospectively);
- Dolutegravir and emtricitabine plasma concentration for patients on ARV regimen containing at least DTG and FTC (performed retrospectively);
- Dolutegravir and emtricitabine plasma concentration if HIV-1 RNA measurement  $\geq 100$  copies/ml in plasma
- Genotypic resistance test if 2 consecutive HIV-1 RNA measurements  $\geq 100$  copies/ml in plasma;
- Pharmacogenetic analyses if 2 consecutive HIV-1 RNA measurements  $\geq 100$  copies/ml in plasma only for patients included in the SHCS and who have signed a consent form for genetic studies (performed retrospectively);
- Urinary  $\beta$ -HCG in women of childbearing potential.

*Costs assessments*

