### 11.2 Determination of Sample Size

The first sample size calculation was based on the primary outcome for the comparison between DTG + FTC dual therapy and standard cART, i.e. the comparison between the proportions of patients in the two arms maintaining virologic suppression, using a two-sample proportion test (96). The following assumptions were made:

- Power 80%
- Significance level 0.025 (one-sided Z test of non-inferiority)
- 97% of patients with conventional cART will be virologically suppressed at week 48 (<100 copies/ml)
- 94% of patients on DTG + FTC dual therapy will be virologically suppressed at week 48 (<100 copies/ml)
- Non-inferiority margin of 12% (as in previous non-inferiority trials)(97-104). We chose 12% noninferiority margin because there is no difference in terms of resistance acquisition between 10% and 22% virological failure.

Sample size of 83 patients in each group (total sample size, 166 patients) to achieve 80% power to detect a non-inferiority margin difference between the group proportions of -0.12 was calculated. The power was computed for the case when the actual cART group proportion is 97% and the actual DTG + FTC dual therapy group proportion is 94%. To allow for at least 10% loss to follow-up and also for the randomisation in two steps in this 1:1:1:1 trial, we will aim to recruit **a total of 184 patients**.

The second sample size calculation was based on the primary outcome for the comparison between simplified monitoring and standard monitoring, i.e. the comparison between mean direct costs in the two arms (105). The following assumptions were made:

- Significance level 0.05 (two-sided t-test)
- Direct costs are CHF 25,000 per year (standard deviation (SD) CHF 8,000) with conventional monitoring
- SDs are equal in the two groups (CHF 8,000)

With sample sizes of 92 patients in each group, we will have approximately 55% power to detect a 10% difference in costs, and 99% power to detect a 25% difference in costs. We will also have substantial power to detect small-to-moderate differences in many of the secondary outcomes, e.g. changes in CD4 cell counts or health-related quality of life. The exceptions are rare outcomes such as adverse events, resistance or clinical complications for which the statistical power to detect differences will be low.

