Time to loss of virological response (TLOVR) will be graphically depicted by Kaplan-Meier curves, and evaluated by a univariable and multivariate Cox proportional Hazard model, adjusted for stratified for the type of monitoring and type of treatment.

Predictors of virological failure (nadir CD4 count, baseline HIV-DNA, zenith HIV-RNA, years since HIV infection, years of viral suppression, CD4/CD8 ratio, age, DTG and FTC plasma concentrations, pharmacogenetic analysis, any other relevant clinical or laboratory parameters) will be assessed using forward stepwise multiple logistic regression.

Economic analyses will be performed from the health provider perspective. A multiple linear regression model will be performed to compare the mean direct costs between the two monitoring strategies after adjustment for the treatment arm.

All analyses will be performed in the PP dataset and in the ITT dataset.

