### 13. POST-STUDY

The study period ends at the week 48 visit or at the study discontinuation visit.

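### A withdrawn patient's cost total closes at the discontinuation visit, but the co-primary cost comparison takes no account of time observed

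*Protocol*

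**What the plan says.** Section 5.1 makes direct cost at week 48 the second primary outcome, comparing patient-centred with standard monitoring. Four places fix the period over which it accrues:

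- Section 9.2.1: "costs will be measured starting from the baseline visit for the complete study period". On source and timing it adds: "Costs will be obtained from health-care insurance of the participants and from trial accounting and collected at week 48".
- Section 13: "The study period ends at the week 48 visit or at the study discontinuation visit".
- Section 8.5: withdrawn participants are asked to a close-out visit "where all assessments planned at week 48 will be done".
- Section 9.3.7 covers week 48 "or study discontinuation visit at SHCS center" and ends with the cost assessment.

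For the analysis, section 11.4.2 uses a multiple linear regression to "compare the mean direct costs between the two monitoring strategies after adjustment for the treatment arm", in both the per-protocol and the intention-to-treat sets. Section 11.4.1 puts every randomised patient in the latter. Section 11.2 plans on "Direct costs are CHF 25,000 per year" with an SD of CHF 8,000. Section 11.5 excludes patients from continuous outcomes when nothing is available at weeks 36 and 48. It does not name costs, and it does not say whether a total taken at a discontinuation visit counts as week-48 data.

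**The concern.** Cost accumulates with time. Section 3.1 puts triple-therapy drugs alone at CHF 14,000 to 22,000 per year, which is 56% to 88% of the planning figure of CHF 25,000. A total that closes at week 12 is therefore roughly a quarter of a completer's total. Entered beside full totals with no term for time observed, it registers leaving the study as a saving. It is also not the annual cost on which the comparison was powered.

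The trial is open-label and the monitoring arms differ in visit burden, so withdrawal could differ between them. If it does, the answer on a primary outcome depends partly on who left. The comparison has little power to spare: the plan itself gives about 55% for a 10% difference.

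**Working it through.** **Inputs from section 11.2.** Mean CHF 25,000 per year, SD 8,000, 92 per arm, two-sided 5% t-test. The target difference is 10%, or CHF 2,500.

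**The plan's own figure.** The standard error is 8,000 × √(2/92) = 1,180, so the noncentrality is 2,500/1,180 = 2.12. Power is 0.56, against about 55% stated. For a 25% difference (CHF 6,250), power is above 0.999, against 99% stated. Both reproduce. The 92 per arm is 184/2, so this power presumes a full year of cost from every randomised patient.

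**Assumptions that the protocol does not give.** A proportion w of each arm supplies a truncated total. Observed cost is annual cost × F, where F = 1 for completers and F is uniform on (0, 1) for leavers.

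- E(F) = 1 − w/2
- E(F²) = 1 − w + w/3
- Mean = 25,000 × E(F)
- Variance = E(F²) × (25,000² + 8,000²) − mean²

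**Equal withdrawal, w = 10% in both arms.**

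- Mean = 25,000 × 0.95 = 23,750
- Variance = 0.9333 × 689,000,000 − 23,750², so SD ≈ 8,890
- A true saving of CHF 2,500 appears as 0.95 × 2,500 = 2,375
- Noncentrality = 2,375 / (8,890 × √(2/92)) ≈ 1.81, so power is about 44%
- There is no false saving, and the type I error stays at 5%

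With gamma-distributed costs whose SD shrinks with the mean, simulated power falls from 61% to 48%. The loss is of the same order.

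**Unequal withdrawal.** Bias = 25,000 × (1 − mean fraction observed) × difference in w. With half of follow-up observed on average, this is 25,000 × 0.5 × 0.01 = CHF 125 per percentage point. If the mean fraction observed is 0.75 or 0.25, it is CHF 62.5 or CHF 187.5. The splits below are illustrative, with no true cost difference:

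| Truncated totals by arm | False saving in the arm with more leavers | Two-sided type I error |
|---|---|---|
| 10% v 10% | 0 | 5% |
| 8% v 12% | CHF 500 | 6–7% |
| 6% v 14% | CHF 1,000 | about 12% |

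In the other direction, take 14% in the standard arm, 6% in the patient-centred arm and a true saving of CHF 2,500. The expected means are 25,000 × 0.93 = 23,250 and 22,500 × 0.97 = 21,825. The visible saving is CHF 1,425 and power is about 20%.

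**If section 11.5 governs costs.** Leavers with nothing at weeks 36 and 48 are removed. Losing 10% leaves 83 per arm and power of about 52%. The comparison is then among stayers, and a patient leaving between weeks 36 and 48 may still carry a short total.

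**The case against.** The strongest reply is that truncation is inferred by joining sections. Section 9.2.1 says that costs are collected at week 48, the visit schedule marks the cost assessment only in that column, and insurer data do not depend on attendance. One could therefore read the plan as costing everyone to week 48. That reading is possible, but it conflicts with sections 13, 8.5 and 9.3.7, and nothing provides for an insurer request running beyond withdrawal. A statistical analysis plan not seen here might annualise costs or handle censoring. The protocol nevertheless already fixes the period and the model for a primary outcome.

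Several limits do stand:

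- A reader might infer that the plan as written must favour the arm with more leavers by a known amount. It does not. Bias needs unequal withdrawal or timing, and the protocol gives no split or direction.
- A reader might count the whole 10% loss to follow-up of section 11.2 as truncated totals. A patient lost without a discontinuation visit has a missing cost, not a short one. Patients who stop only the study drugs generally stay to week 48 (section 7.4).
- A reader might say that the hypothesis is stated per year. Section 11.1 gives it no time unit; only the planning assumption in section 11.2 is annual.
- The ±21-day window at week 48 might look like a further source of distortion. If visits are uniform over it, the SD of follow-up is 6/√12 = 1.73 weeks, or 3.6% of 48 weeks (about CHF 900). That moves the SD from 8,000 to about 8,050, equally in both arms, which is negligible.
- The per-protocol set removes most early treatment stoppers, so the problem lies mainly in the intention-to-treat set.

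**Conclusion.** The point holds in a conditional form. Followed as written, the protocol enters a shortened cost total for a patient who withdraws and attends the discontinuation visit, and compares it with full totals without regard to time observed. The alternative, section 11.5, drops most early leavers and departs from the all-randomised set. The protocol does not say which applies.

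With equal withdrawal the consequence is lost power only, from about 56% to about 44% at an assumed 10% of truncated totals with uniform timing. With unequal withdrawal the bias is about CHF 125 per percentage point of imbalance, if leavers are observed for half of follow-up on average. It can go either way. The documents do not support a claim that the result will be biased, only that the rule leaves a primary outcome open to it when a simple remedy exists.

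**What to change.** In sections 9.2.1 and 11.4.2, define the outcome as direct cost from baseline to a fixed 48 weeks for every randomised patient. Request the insurer statement to that date whether or not the patient still attends, unless consent to data collection is withdrawn.

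Do not enter truncated totals as full 48-week costs. For the remainder, pre-specify a censored-cost method, for example inverse-probability-of-censoring weights, with cost per week observed as a sensitivity analysis. State in section 11.5 how its rule applies to costs.

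The insurer letter is already a source document (section 12.1.2), so the change needs wording and a dated request. It costs a slightly later data cut for leavers and a little more analysis. Where consent to data collection is withdrawn, the request recovers nothing and the censored-cost method has to carry those patients.
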